### Power

We estimate that under care as usual the estimated average percentages of school absence, our primary endpoint, at the end of follow-up, will be 40%. Given the efficacy of face to face CBT in adolescence [3] we consider a reduction of school absence of 15% in the e-intervention group to be realistic and highly relevant. In order to statistically detect such a reduction, given a 2 sided-alpha of 0.05 and with 90% power, we will need to allocate 60 patients to each group. In order to accommodate a small anticipated percentage of non-participation we will include 140 diagnosed patients.

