**Methods/Design:**

A randomized clinical trial is currently conducted. One-hundred-forty adolescents aged 12-18 years diagnosed with CFS will be recruited and randomized to one of two groups: FITNET or usual care. After 6 months, the usual care group will have access to the FITNET program. Outcomes will be assessed at baseline, post intervention, and at 6 months follow-up. Primary outcome measures are school presence, fatigue severity, and physical functioning.

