**Possible parental predictors of treatment outcome**					

Fatigue severity	Checklist Individual Strength (CIS subscale fatigue) [19]	X			

Psychological distress	Symptom Checklist (SCL-90) [30,31]	X			

Focussing on bodily symptoms	subscale private body consciousness of the Body Consciousness Scale [32,33]	X			

Perceptions of rearing behaviours	EMBU-P [34]	X			

Causal attributions	CAL [19]	X			

The primary outcome measures are: (1) Fatigue as measured by the subscale *fatigue severity *(8 items, 7-points Likert Scale) of the Checklist Individual Strength-20 [19] with a severity range from 8-56. The questionnaire has good reliability and discriminative validity. (2) Physical functioning as measured by the subscale *physical functioning *(9 items) of the validated Dutch translation of the Child Health Questionnaire (CHQ-CF87) (0-100%) [20], and (3) School presence (expressed in attended hours/obliged hours * 100%) as assessed in prior intervention studies in adolescents with CFS[3]. Secondary outcome measure is self-rated improvement, measured using a short questionnaire consisting of 4 items as assessed in prior intervention studies in adolescents with CFS [3]: patients indicate whether they have completely recovered, feel much better, have the same complaints of have become worse compared with the previous measurement.

Outcome measures will be obtained at the UMCU at the start of the study period (T0), after the intervention 6 months later (T1) and after 6 months follow-up (T2). For those adolescents primarily allocated to usual care who will start with FITNET at T1 - in case of no recovery - there will be an extra follow-up moment after 12 months (T3), *see figure *1.

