### Statistical Analysis

One-hundred-forty newly diagnosed CFS patients will be included in two years. The data will be analysed on an intention to treat basis. Prognostically important baseline characteristics will be tabulated by treatment modality in order to evaluate success of randomisation. The main efficacy analysis will pertain to the data obtained after a 6 months FITNET or usual care condition. Differences between treatment groups concerning the primary outcome measures will be expressed as relative risks and 95% confidence intervals or as central estimators and variance measures where appropriate. In case of baseline differences in prognosis between groups, treatment effects in primary outcome will additionally be adjusted for these differences using logistic regression for binary outcome data and linear regression for continuous outcome measures. At 12 months follow-up after randomization, a repeated measurement of the primary outcome measures will be undertaken as well as an evaluation of participants' experiences with the FITNET intervention. The latter measurements will have a descriptive nature.

Concerning the predictors of outcome, the study will be merely exploratory because statistical power is not calculated for subgroup analyses. To that end, linear regression analysis will be used with primary continuous outcome measures as dependent variables and interaction terms of putative response predictors and treatment modality as independent variables. Separate analyses will be run for predictors in adolescents and predictors in parents respectively.

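### The outcome sections name three unranked primary outcomes, but the Power section calls school absence alone the primary endpoint and gives it the whole 5% and 90% power

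*Protocol article*

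**What the plan says.** The Abstract (Methods/Design) lists three: "Primary outcome measures are school presence, fatigue severity, and physical functioning". Table 2 puts the same three under its primary heading, with fatigue first and school presence last. The Outcomes text numbers them in Table 2's order, beginning "The primary outcome measures are: (1) Fatigue as measured by the subscale", and school presence is again third. None of these places ranks the outcomes for testing, and the Abstract's order differs from that of Table 2 and the Outcomes text.

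The Statistical Analysis section keeps the plural: "Differences between treatment groups concerning the primary outcome measures will be expressed as relative risks and 95% confidence intervals", or other summaries where suitable.

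The Power section speaks of one endpoint. It assumes that "the estimated average percentages of school absence, our primary endpoint, at the end of follow-up, will be 40" per cent under usual care, and it sizes the trial on a 15% reduction "given a 2 sided-alpha of 0.05 and with 90% power". The result is 60 patients per group, raised to 140 in total.

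On timing, the Power section refers to the end of follow-up. The Study design and Statistical Analysis sections put the main efficacy comparison at 6 months. Statistical Analysis plans a repeat measurement at 12 months after randomisation, and the usual care group is offered FITNET from 6 months.

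**The concern.** The article states one aim, to determine whether FITNET is efficacious, but gives two accounts of which outcome decides it. Three answers fit the text: school presence alone, any one of the three, or all three. Each has a different false-positive rate and a different power, and the figures in the Power section belong only to the first.

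The trial is open to the participants, and the outcomes are questionnaire scores and attendance. If the deciding outcome is not fixed before the data are seen, the choice could follow the results. The outcome that sized the trial stands last in the list that defines the outcomes, so a reader cannot recover a hierarchy from the order of listing.

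**Working it through.** **Inputs.** From the Power section: two-sided alpha 0.05, power 90%, 60 per group, usual care mean absence 40%, reduction 15%. From the Abstract, Table 2 and Outcomes: three primary outcomes. Not stated: the SD of school absence, whether the 15% is absolute or relative, power for the other two outcomes, and the correlations between outcomes.

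**The plan's own figure.** For a difference in means, n per group = 2(1.960 + 1.282)² SD² / d². With d = 15 points and n = 60, SD = 15 × √30 / 3.242 ≈ 25.3. The stated 60 is therefore consistent with a comparison of means at an SD of about 25, but it cannot be confirmed because no SD is given. What matters here is that the calculation covers one outcome at the full 0.05.

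**Reading 1: school presence alone decides.** Error is 5% and power is 90%, as stated.

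**Reading 2: any one of three at 0.05.**
- Independent outcomes: 1 − 0.95³ = 0.1426, or 14.3%. This is the maximum for jointly normal two-sided test statistics.
- Equal pairwise correlation (assumed), simulated with 1,000,000 draws each: 13.6% at 0.3, 12.5% at 0.5, 10.9% at 0.7.
- These rates count errors in both directions. In favour of FITNET only, under independence: 1 − 0.975³ = 0.073, or 7.3%, against 2.5% for a single test.

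**Reading 3: all three required.** Error is at most 5%, because every test must reject. Joint power is at most that of the weakest outcome. Power is stated for school absence only, so the document gives no value for joint power.

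**Cost of keeping three primaries.** A test with 90% power at two-sided 0.05 has an expected statistic of 1.960 + 1.282 = 3.242. At alpha/3 = 0.0167 the critical value is 2.394, so power = Φ(3.242 − 2.394) = Φ(0.848) ≈ 0.80. The SD does not enter this step. Holm tests at alpha/3 only at its first step, so 80% is a lower bound for school presence under Holm.

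**The case against.** The strongest reply is that the article states no any-one-of-three rule. The Statistical Analysis section describes how differences will be reported, not what counts as success. The only alpha statement in the document attaches to school absence, and on that reading the error is 5%. The article also condenses a fuller protocol, and a multiplicity rule could properly sit there or in an analysis plan that is not shown.

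Most of this stands. A reader might infer that the trial carries a 14% false-positive risk, or that it has no success rule anywhere. The documents support neither: the first needs a rule that no section states, and the second would treat an article's silence as a gap in the plan. A reader might also take joint power to be about 73% (0.9³), but that assumes independence and 90% power for fatigue and for physical functioning, which the article does not give.

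It can also be said that school presence is not the obvious choice. Every patient must meet the fatigue threshold to enter, whereas the inclusion criterion on physical functioning and school participation is and/or, so a patient may enter without a school deficit. That bears on which outcome the team should choose.

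The contradiction itself remains. The text asserts both three primary outcomes and one, and naming the primary endpoint is a matter for the protocol. An unseen plan could add a rule, but it would not make these sections agree.

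**Conclusion.** The point holds as a conflict within the current text. The stated 5% and 90% apply to the efficacy claim only if school presence alone decides it. The other readings show what depends on the choice:
- Any one of three at 0.05: two-sided family-wise error of about 11% to 14% for correlations from 0.7 down to 0, with about 7% in favour of FITNET under independence.
- All three required: error of 5% or less, with power below or equal to that of the weakest outcome and not derivable from the article.

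These are conditional illustrations; they rest on assumed correlations and jointly normal test statistics. They do not show that the trial as planned has an inflated error rate, and they do not show that 60 per group is wrong. The time point of the endpoint is a second, related inconsistency.

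**What to change.** Make the Abstract, Table 2, Outcomes, Statistical Analysis and Power sections agree before any analysis, in one of two ways.

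1. Name school presence at 6 months as the single primary endpoint at two-sided 0.05. This matches the sample size and leaves it unchanged. Fatigue severity and physical functioning become secondary, or are tested in a pre-stated order. The cost is that formal claims on those two become conditional on the school result or are given up, which matters because fatigue is the symptom that every patient must have to enter.
2. Keep three primaries under Holm, and restate the power for school presence as at least about 80% with 60 analysed per group. The cost is lower stated power, and power for the other two outcomes would have to be given as well.

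In the same edit, replace the Power section's reference to the end of follow-up with the time point of the main efficacy analysis, which the Study design and Statistical Analysis sections put at 6 months. Under the first option the whole change is wording.

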## Discussion

To the best of our knowledge, the FITNET study will be the first randomized clinical trial which evaluates the effect of web-based treatment versus usual care in adolescents with CFS.

This study has several strengths. Firstly, the FITNET treatment is based on a theoretical model of a proven effective face-to-face CBT for adolescents [3] and will be compared with usual care in a randomized design. This will enable to determine the additional value of FITNET in the current therapeutical spectrum. Secondly, FITNET involves parents in the treatment of adolescent CFS. Earlier studies from Chalder et al showed the importance of family-focused CBT to achieve treatment success in adolescents [4,35]. Furthermore, the advantage of making treatment available at any time by internet is considerable. Online treatment can reduce face-to-face treatment barriers (i.e., inconvenience of scheduling appointments, missing school/work, travelling to and from a clinician's office) [36,37], increase adherence [38] and reduce treatment time and costs[37]. We hope that a web-based treatment will increase the therapeutic accessibility. A limitation of the study is that the design is not appropriate to compare the efficacy of web-based CBT with face-to-face CBT. That would have asked for a non-inferiority design with comparison of the two interventions.

In conclusion, the FITNET study will provide greater insight on evidence-based treatment options for adolescents with CFS. If web-base CBT is more effective than usual care, this web-based program would greatly improve the prognosis of the adolescents with CBT.

## Abbreviations

CBT: Cognitive Behavioural Therapy; CDC: Centre for Disease Control and Prevention; CFS: Chronic Fatigue Syndrome; CIS-20: Checklist Individual Strength; CHQ-CF87: Health Questionnaire-Child Form; ECCF: Expert Centre for Chronic Fatigue; RCT: Randomized Controlled Trial; UMCU: University Medical Centre Utrecht.

## Appendix 1: Overview of FITNET web-based CBT treatment for adolescents with CFS

### *Psycho-educational part*

What is CFS?

CFS in the Netherlands

CFS in my family

Causes of CFS

CFS, anxiety, depression and other illnesses

How is the diagnosis confirmed?

What is the treatment for CFS?

Talking about CFS/How do I explain what CFS is?

Future forecast

### Cognitive Behavioural Treatment Modules

1. To introduce myself

2. How does this treatment work?

3. Assessing my present possibilities

4. My parents

5. My goals

6. My sleep routine

7. My thoughts

8. Changing my attention to fatigue

9. Step up my physical activities (*passive patients*)

10. Balance between activity and rest (*relative active patients*)

11. Step up my physical activities (*relative active patients*)

12. Recognizable problems with the treatment

13. Step up my mental activities

14. My schedule for school

15. My social activities

16. To reach goals

17. My schedule for work

18. To have a night out

19. Do I still see myself as a patient with CFS?

20. My evaluation

21. Follow-up

FITNET is derived from the protocol for CBT that was developed on the basis of a model of perpetuating factors of CFS[2]. It has been tested in several studies [3,17,39] and is aimed at changing fatigue related cognitions and a gradual increase of activities.

Typically, treatment involves (a) formulation of treatment goals, (b) establishing a sleep routine, (c) encouraging the participant to achieve a balance between activity and rest, (d) gradually increasing activities including home, social and school life, (e) addressing cognitions about fatigue, (f) gaining independence from surroundings and parents, (g) reducing the focus on fatigue, and (h) paying attention to relapse prevention.

Addressing physical activity patterns is important in CBT for adolescent CFS. The CBT modules are adapted for two levels of physical activity: relative active and passive, based on the existing protocols[3,16,17]. An actometer, a motion sensing device that can quantify physical activity, will be used to assess the activity pattern [27,32]. Adolescents with a *relatively high physical activity pattern *alternate between periods of activity and periods of rest[16]. For these patients the therapy focuses on learning to recognise and accept their current state of fatigue and impairment. Then they learn to distribute their activities more evenly. After this, the patient will start to build up activity levels. In contrast, patients with a *low physical activity pattern *spend most time lying down and go out infrequently. Most do not attend school at all. For them, the treatment program starts with a systematic build up of activity as soon as possible, while addressing and challenging their beliefs that activity would aggravate symptoms.

Modules 1, 2 and 4 introduce CBT and explain the role of the therapists, and the context of the family. A rationale based on a multi-factorial model of CFS that distinguished predisposing, precipitating and maintaining factors is presented. Parents will be actively involved in supporting their child and parents' beliefs and behaviours regarding the condition of their child will be explored and addressed. The aims of therapy take into account the specific developmental tasks of adolescents. In children younger than 15 years, parents often act as a coach; for older participants, parents have to step back and encourage their child to take responsibility for the treatment.

Modules 3 and 5 are focused on treatment goals. Return to full time education is always a goal of treatment, and a plan for returning to school will be discussed early with everyone involved.

Modules 6 to 19 focus on cognitive behavioural strategies and include instructions and exercises on how to identify, challenge and change cognitive processes that contribute to CFS. There are two treatment protocols, depending on the pattern of physical activity of the patient[16].

Module 20 evaluates treatment success.

Module 21 is a relapse preventing module focusing on maintaining gains and staying healthy.

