### Randomization and blinding

Concealed randomisation will be performed by the data-management section of the Julius Centre for Health Sciences and Primary Care Utrecht. This randomization is computer-generated by creating 'blocks' with a size of 6, ensuring that the same number of participants will be allocated to each group. The investigators who are responsible for the inclusion will be blinded. Primary outcome parameters will be assessed by computer.

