**Possible patient's predictors of treatment outcome**					

Depression score	Child Depression Inventory (CDI) [21,22]	X			

Anxiety score	Spielberger State-Trait Anxiety Inventory for Children, STAIC [23,24]	X			

Somatisation score	Children's Somatisation Inventory (CSI) [25,26]	X			

Physical activity	Actometer and Self-observation list daily functioning [27,28]	X	X	X	

Self-efficacy	Self Efficacy Scale-28[2]	X			

Perceptions of parental rearing behaviours	EMBU-A [29]	X			

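### Baseline activity pattern selects the FITNET protocol and is tied to school attendance, yet the 6-month comparison does not prespecify it as a covariate

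*Protocol article*

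**What the plan says.** All references are to the protocol article.

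- **Two protocols.** Appendix 1 (Cognitive Behavioural Treatment Modules) states: "There are two treatment protocols, depending on the pattern of physical activity of the patient", and also: "The CBT modules are adapted for two levels of physical activity: relative active and passive". Module 9 is labelled for passive patients, and modules 10 and 11 for relatively active ones. The actometer "will be used to assess the activity pattern". No cut-off is given.
- **Link to the endpoint.** Of patients with a low activity pattern, the same appendix says: "Most do not attend school at all". The Power section sizes the trial on school absence.
- **Data collected.** Table 2 lists "Actometer and Self-observation list daily functioning" at T0, T1 and T2 among the possible patient predictors, with no restriction to one arm.
- **Allocation.** Randomization and blinding says: "This randomization is computer-generated by creating 'blocks' with a size of 6". It names no stratification factor.
- **Analysis.** Under Statistical Analysis, the main comparison is by intention to treat at 6 months. Regression adjustment is an addition, made in the event that the groups differ in baseline prognosis. The predictor analysis is a linear regression with "interaction terms of putative response predictors and treatment modality as independent variables", and is declared exploratory and unpowered.

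**The concern.** A baseline variable that the article itself ties to non-attendance is left out of both the allocation scheme and the main model. Two things are at stake.

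First, a strong prognostic covariate that is omitted leaves its variance in the error term, so the treatment effect on school presence is estimated less precisely than the data allow. Making adjustment conditional on an observed imbalance also means that the set of reported estimates depends on the data.

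Second, inside FITNET the pattern decides which protocol is delivered; in usual care it does not. An activity-by-treatment term therefore combines how a patient's activity relates to response with which protocol was received. If such a term is reported as activity predicting response, it says more than the design can support. Finding predictors is the trial's second stated goal.

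**Working it through.** **The plan's own figure.** The Power section gives 60 per group for a 15% reduction from 40% absence, two-sided alpha 0.05 and 90% power. It states no SD and does not say whether the 15% is absolute. Read as a 15-point difference in means, n = 2(1.96 + 1.2816)² SD²/15² = 60 requires SD = 15/(3.2416 × √(2/60)) ≈ 25.3. Read as proportions of 40% and 25%, 203 per group would be needed. The means reading with an SD near 25 is used below. The point does not depend on it.

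**Assumptions (not in the article).** Passive share p = 25% (range 15% to 40%); 6-month absence higher by g = 30 points in passive patients (range 20 to 40); SD 25; 60 analysed per arm.

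**Variance explained by the pattern.** Between-pattern variance = p(1 − p)g².

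| p | g | p(1 − p)g² | Share if 25 is the total SD | Share if 25 is the within-pattern SD |
|---|---|---|---|---|
| 0.25 | 30 | 168.75 | 168.75/625 = 27% | 168.75/793.75 = 21% |
| 0.15 | 20 | 51 | 51/625 = 8% | 51/676 = 8% |
| 0.40 | 40 | 384 | 384/625 = 61% | 384/1009 = 38% |

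**Effect on precision.** The unadjusted standard error with total SD 25 is 25 × √(2/60) = 4.56 points. With the covariate it is about 4.56 × √(1 − R²): 4.56 × √0.73 = 3.90 in the central case, 4.56 × √0.918 = 4.37 at the low end and 4.56 × √0.386 = 2.83 at the high end.

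**Chance imbalance.** The SD of the difference in passive share is √(2 × 0.25 × 0.75/60) = 7.9 percentage points. The arms differ by 10 points or more in about 25% of trials at 60 per arm, and 20% at 70 per arm. A 10-point imbalance moves the estimate by 0.10 × 30 = 3 points. That is 3/15 = 20% of the target if the target is absolute, and 3/4.56 ≈ 0.66 of one standard error.

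**Activity-by-treatment term.** Suppose the effect is 15 points in active and 0 in passive patients, activity has no influence within a protocol, there are 70 per arm and the SD is 25.3. At passive shares of 10%, 25% and 50%:

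- a continuous activity score gives a significant interaction in 9%, 19% and 29% of simulated trials (about 5% when the two effects are equal);
- a binary active/passive indicator would do so in 18%, 33% and 42% (normal approximation).

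A difference arising wholly from the protocols can thus appear as a patient predictor under either coding. The binary form only detects it more often; it does not separate the two explanations.

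**The case against.** The strongest defence is that the trial answers the question it asks. The Background sets the primary aim as the efficacy of FITNET, a tailored programme, against usual care. Only three of the 21 modules are labelled as pattern-specific. Chance imbalance under randomisation is not bias, ordinary standard errors already cover it, and the plan tabulates baseline characteristics and allows adjustment. The predictor work is openly called exploratory. All of this stands.

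Stronger readings are tempting and are not supported:

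- **That the pooled effect is misleading because it hides which protocol works.** The trial does not claim to show this. By-pattern results could not show it either, since within FITNET pattern and protocol coincide; separating them would need randomisation to protocol within pattern.
- **That the pattern is ignored in the analysis.** An activity-by-treatment term is already planned.
- **That a linear activity score blurs the step between protocols.** The article specifies linear regression, which accepts a binary predictor. How activity is coded is not stated and may properly be left to an analysis plan.
- **That the blocks must be stratified.** Stratification would require the twelve-day actometer recording to be finished and classified before allocation, and covariate adjustment secures most of the benefit.

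Two parts of the defence do not fully answer the point. The conditional adjustment rule is stated in the article, so it is not a detail left open; it forgoes the precision gain whenever the arms look balanced. The exploratory label concerns power, whereas the overlap of pattern with protocol would remain at any sample size.

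**Conclusion.** The concern holds in a limited form. The primary comparison is valid and unbiased for FITNET as a whole. It leaves unused a baseline variable that the article itself links to school attendance, and it makes adjustment depend on what the baseline table shows. Under the central assumptions the covariate accounts for 21% to 27% of the variance in school absence. With 25 as the total SD, the standard error falls from 4.56 to about 3.90 points.

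The size is uncertain: the passive share, the gap and the SD are all assumed, and the explained share runs from 8% to 61% over the range. The gain would be smaller if baseline school presence, also measured at T0, were in the model, since the two overlap. The article documents the link for school attendance only, so no figure is offered for fatigue or physical functioning.

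For the second aim, an activity-by-treatment finding can be described but cannot be attributed to activity as a patient characteristic.

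**What to change.** 1. Derive the relatively active/passive class for every patient in both arms from the T0 actometer, by the same rule that is used to choose the protocol, and without knowledge of arm. Write that rule down, and confirm that the recording precedes the start of treatment.
2. Include the class as a prespecified covariate in the 6-month comparison, whether or not imbalance is seen, in place of adjustment triggered by baseline differences.
3. Report any activity-by-treatment term, binary or continuous, descriptively and as an effect of FITNET as delivered. State that activity as a patient predictor cannot be separated from the protocol received.

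Stratified blocks are not needed, and no claim should be made about which protocol works. The cost is one derived variable from data already collected, a slightly larger model and a few sentences of analysis text. Treatment, sample size and visits are unchanged.
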